### Interim analyses {21b}

For ethical and safety reasons, an interim analysis will be performed after enrolment of 42 (50%) patients. The purpose of this analysis is to ensure that the rates of adverse events are within acceptable limits (within the normal rate of complications related to PRC/FCA). The interim analysis will be carried out blinded to the group allocation unless a clear deviation in the incidence of AEs is found, in which case the allocation will be unveiled, and the study discontinued.

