Although several studies report the outcomes of PRC and FCA, there is a paucity of high-quality evidence that would support the use of one technique over another. Two RCTs exist comparing these techniques [6, 7]. However, these trials suffer from methodological shortcomings, such as lack of blinding, high risk of selection bias, and incomplete outcome reporting. Generally, studies show no significant difference in ROM, grip strength, pain, or patient-rated outcomes [6–8]. However, some study groups suggest that FCA may be superior in terms of grip strength, while PRC may be preferable in terms of ROM, postoperative complications, and secondary operations [9–12]. Some studies indicate that PRC is more cost-effective [13, 14], while Daar et al. [15] concluded that FCA with cannulated compression screws is the most cost-effective approach. A long-term study reported fewer arthritic changes after FCA versus PRC. However, there was no apparent correlation between radiographic OA and patient satisfaction [16].

The most recent meta-analysis comparing PRC and FCA from Kamir et al. (2020) used flexion/extension ROM, grip strength, and pain level as outcome measures. They found that PRC was statistically but not clinically significantly better than FCA in all outcome measures [17].

Wrist OA due SLAC- and SNAC-degenerative pattern remains a common disorder encountered by a wrist surgeon. To date, most surgeons will choose to manage patients with SLAC/SNAC OA with FCA over PRC. However, the use of PRC has gained popularity among clinicians due its simplicity and predictable results, without the need to remove hardware or control for bony union. We hypothesize that PRC is non-inferior to FCA with lower economic expanses. While superiority of either procedure may be insurmountable to present, a thorough assessment of important considerations, such as AEs, postoperative pain, ROM, and convalescence time, should be examined by means of a randomized controlled trial (RCT). Thus, we planned a study protocol for a multicenter, double-blinded, randomized controlled non-inferiority trial comparing PRC vs FCA for the treatment of SLAC/SNAC I-II OA of the wrist.

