### Sample size {14}

The primary outcome measure is PRWE and the primary hypothesis of our trial is that PRC is non-inferior to FCA in the treatment of SLAC/SNAC OA I-II measured with PRWE total score. The non-inferiority margin is set at 11.5 points using the PRWE minimally clinically important difference [31]. To exclude the non-inferiority margin, the trial will require 37 patients in each group to observe MCID (non-inferiority margin 11.5, SD 14) in PRWE scores between the trial groups with a power of 90% and using a one-sided type I error rate of 2.5%. We will recruit 84 patients to account for 10% loss during follow-up.

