## Assignment of interventions: allocation

### Sequence generation {16a}

A randomization sequence will be generated using an internet-based program (sealedenvelope.com). Patients will be allocated to one of the two treatment groups in a 1:1 ratio using permuted block randomization with variable block size.

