### Composition of the data monitoring committee, its role and reporting structure {21a}

The Helsinki university central hospital (HUCH) institute is responsible for (1) clinical onsite monitoring according to EN14155 and maintaining (2) a written “investigator file” and (3) a monitoring manual to ensure patient’s rights, patient’s security, and reliability of trial results. The trial sites will be visited onsite by a clinical research associate before study initiation. During the trial, sites will be monitored at regular intervals depending on the rate of recruiting and data quality using onsite visits and video meetings. A monitoring log is used to document all visits completed by the research associate from HUCH institute.

Moreover, a data safety and monitoring committee (DSMC) will be established. The DSMC consists of a clinician familiar with SLAC/SNAC treatment, a clinician familiar with clinical trials, and a statistician. The DSMC will evaluate the safety of the trial based on major adverse event reporting.

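### The interim safety rule stops the trial on allocation-blinded adverse event data, with no review by arm before the decision

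*Protocol article*

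**What the plan says.** The section Interim analyses {21b} fixes four things.

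- **Timing:** "an interim analysis will be performed after enrolment of 42 (50%) patients".
- **Benchmark:** adverse event rates should be "within the normal rate of complications related to PRC/FCA".
- **Blinding:** "The interim analysis will be carried out blinded to the group allocation unless a clear deviation in the incidence of AEs is found".
- **Consequence:** "in which case the allocation will be unveiled, and the study discontinued".

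The section names no role that runs the look or takes the decision. Under Composition of the data monitoring committee {21a}, a DSMC of two clinicians and a statistician is set up, and "The DSMC will evaluate the safety of the trial based on major adverse event reporting". Adverse event reporting {22} has major events reach that committee within 5 working days.

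The Adverse events paragraph under Secondary outcomes counts non-union and implant-related complications as adverse events. The Discussion says that proximal row carpectomy (PRC) avoids these risks. The Background reports that some study groups suggest "PRC may be preferable in terms of ROM, postoperative complications, and secondary operations".

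**The concern.** A safety look at mid-recruitment should let someone judge whether one procedure is doing unexpected harm, and then decide about the trial. Here the order is reversed: the judgement is made without the allocation, and once it is made the trial ends. The data by arm become available when they can no longer change anything.

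This matters in two ways, depending on what blinded means here.

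- **Overall rates.** An excess in one arm is averaged with the other arm and may not show.
- **Masked groups A and B.** The excess shows, but so does any gap between FCA and PRC that the protocol expects. Blinded reviewers cannot tell an expected gap from an unexpected one. A listing by event type would also reveal which group is FCA, so the masking would not hold.

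The benchmark raises the same difficulty. If it means one combined rate, dilution applies. If it means a separate normal rate for each procedure, the reviewers need to know which group is which in order to apply it.

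At stake is a non-inferiority trial of 84 patients that could be ended on a number nobody has interpreted by arm, or that could continue past an excess in one arm.

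**Working it through.** **The plan's own figure.** Sample size {14} recruits 84 in total. 84 × 0.5 = 42, so the stated 50% reproduces. With allocation in a "1:1 ratio using permuted block randomization with variable block size", 42 patients are about 21 per arm.

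**Assumed inputs.** The article gives neither a normal adverse event rate nor a numerical trigger. Both are assumed here:

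- normal rate p0 = 0.15 in each arm;
- pooled flag: smallest r with P(Bin(42, p0) ≥ r) ≤ 0.05;
- by-arm flag: the same rule on 21 patients, at 0.05 (looser) or 0.025 (stricter).

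**Thresholds**

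| Flag | Threshold | False-flag probability | One event fewer |
|---|---|---|---|
| Pooled | 11 of 42 | 0.042 | 0.089 |
| By arm, looser | 7 of 21 | 0.029 | 0.083 |
| By arm, stricter | 8 of 21 | 0.008 | 0.029 |

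**Detection.** The pooled flag is P(X1 + X2 ≥ 11) with X1 ~ Bin(21, p1) and X2 ~ Bin(21, p2) independent. The by-arm figure is P(Bin(21, p1) ≥ 7) or P(Bin(21, p1) ≥ 8) for the arm with the excess.

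| True rates p1 vs p2 | Mean rate | Pooled flag | By-arm flag, 8 / 7 of 21 |
|---|---|---|---|
| 30% vs 15% | 22.5% | 34% | 28% / 45% |
| 30% vs 7.5% | 18.75% | 14% | 28% / 45% |
| 45% vs 15% | 30% | 77% | 80% / 90% |

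When the other arm runs at its normal rate, the pooled flag falls inside the by-arm range (30% vs 15%) or just below it (45% vs 15%). The clear loss comes when the other arm runs below normal, as in the second row.

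If both arms rise to 30%, the pooled flag fires 76% of the time. Flagging either arm gives 1 − (1 − 0.449)² = 70% at the looser limit and 1 − (1 − 0.277)² = 48% at the stricter one. Pooling is therefore better for a harm common to both procedures.

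**What the opened code would show.** Take 30% vs 15% and condition on the pooled flag having fired. Summing over all tables with X1 + X2 ≥ 11, a two-sided Fisher test of the arms gives p < 0.05 in about 18% of cases. In most such stops, the data by arm would not clearly point to one procedure.

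**Follow-up at the look.** From 15 October 2020 to December 2024 (Trial status) is about 50.5 months: 84 / 50.5 = 1.66 patients per month, so 3 × 1.66 ≈ 5 of the 42 would have under three months of follow-up. With the end-2028 date in Recruitment {15}, about 98.5 months, it is 3 × 0.85 ≈ 3. This is a minor effect. The trigger is also worded as enrolment, and Implementation {16c} has patients enrolled before the arthroscopy that precedes randomisation, so a few of the 42 may not yet have been operated on.

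**The case against.** Five points on the other side deserve weight.

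1. **Unveiling is named with discontinuation, and ahead of it.** A reader might infer that the trial stops before anyone has seen which arm is affected. The text does not say that, and the operating surgeons know the allocation throughout. What stands is narrower: the text leaves no decision between opening the code and stopping.
2. **Pooled is an inference.** A reader might take it that the look sees one overall rate only. Masked groups fit the wording equally well, and the Statistical methods section has a biostatistician who works without knowing the assignments. Under that reading the dilution figures do not apply. The fixed stop remains, and the anticipated FCA–PRC gap becomes the problem.
3. **Expected non-unions lie inside the normal rate, so they are no deviation.** This is fair if the benchmark is applied separately to each procedure. A reviewer blinded to allocation cannot do that.
4. **Serious harm has another route.** Complications leading to hospitalisation, re-operation or death reach the DSMC within 5 working days, surgeons read the follow-up scans, and single patients can be unblinded. This look is therefore not the only safeguard, which lowers the stakes.
5. **The article does not exclude the DSMC from the look.** It is silent, and roles and numerical limits may stand in the full protocol or a charter that is not shown. A reader might infer that the DSMC has no part in it, but the silence does not support that. Neither the missing limits nor the unnamed reviewer is the finding. The stated consequence is.

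**Conclusion.** The point holds as a badly fixed decision rule. Discontinuation follows from a finding on allocation-blinded data, and the stated procedure has no review by arm before it. That conclusion rests on the text alone and holds whether the blinded look uses overall rates or masked groups.

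The figures illustrate it and do not measure it. They depend on an assumed 15% normal rate, 21 per arm and assumed flags. The claim that pooling is badly insensitive would be too strong: at 30% vs 15% the comparison is 34% against 28% to 45%, so it can favour either approach. A marked loss (14% against 28% to 45%) appears only if the other arm runs at half its normal rate. Review by arm at this sample size is itself of modest sensitivity. Its main value is that whoever decides to stop does so knowing which procedure has the events and of which kind.

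The enrolment trigger is a minor addition. The change is worth making, since it is cheap and the rule governs whether the trial continues.

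**What to change.** Amend Interim analyses {21b} and align it with the DSMC paragraph in {21a}:

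- State that the DSMC receives the interim adverse event data as a closed report by arm, covering all adverse events and major adverse events, with non-union and implant events shown separately.
- Trigger the report when the first 42 randomised patients have reached one common follow-up visit, named in the protocol.
- Replace automatic discontinuation with a DSMC recommendation made after review by arm, under limits that the DSMC sets in its charter beforehand. Include the overall rate in the report, since it is more sensitive to harm common to both procedures.
- Keep the sponsor, the investigators and the trial biostatistician blinded to the report.

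The cost is protocol wording and a charter entry, because the committee and its statistician are already planned. The look comes slightly later, by the time the last of the 42 needs to reach the chosen visit. No efficacy data are examined, so there is no cost in type I error.

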### Adverse event reporting and harms {22}

AEs will be reported. Moreover, all major AEs will be documented and reported to the DSMC within 5 working days. All AEs occurring during trial participation will be treated according to standard of care.

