Although a growing number of scientific papers have been published comparing these different techniques for FCA, no RCTs have been conducted. Based on non-randomized comparisons, the outcomes seem comparable [10, 15, 38, 39] and long-term outcomes of FCAs are reasonable [12, 40–42]. In this trial, we chose cannulated compression screws for rigid internal fixation to allow early ROM exercises and to ensure concealment of treatment allocation (no implant removal). All four “corners” will be decorticated and fused to achieve generalizable results. Cancellous bone graft is used to enhance ossifying potential [43, 44]. However, the placement, number, diameter, and length of the screws will be left to the surgeons’ discretion without compromising stability of the fixation.

PRC was described in 1944 by Stamm [45] and has regained popularity among surgeons treating wrist OA. The rationale for this procedure is similar to FCA, namely to preserve as much motion as possible while treating pain by relocating contact and motion of the wrist to a healthy articular cartilage. PRC is a rather easy procedure to perform and avoids the risk of bony non-union, implant loosening, breakage, and removal. The long-term outcomes of PRC have previously been shown to be rather good when compared to FCA long-term outcomes [16, 44, 46]. The possible disadvantages are mainly due shortened bony frame, which is hypothesized to cause impaired grip strength and impingement between the trapezium and radial styloid. Moreover, unlike FCA, PRC may not be performed on patients with advanced OA present at the head of the capitate, such in SLAC/SNAC III [19]. In this trial, patients with marked OA of the capitate head will be excluded. As with FCA, a pragmatic approach will be used for PRC, allowing the surgeon to perform radial styloidectomy when deemed necessary.

The pragmatic execution of the procedures will allow the surgeon to treat the patient according to the unique clinical presentation of the condition. However, this might also be interpreted as a limitation, as variation in the technique may potentially affect outcomes. However, we are not aware of any evidence that the modifications would affect the results and the pragmatic setting improves generalization. Another limitation is that the staff in the operation room cannot be blinded to the allocation. This is unlikely to cause performance bias as the surgeon and other operating room staff are excluded from postoperative treatment.

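### The blinded interim adverse-event look is less able to detect an excess in one arm, cannot reliably judge it against that procedure's own norm, and joins unveiling to stopping with no by-arm review between

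*Protocol article*

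**What the plan says.** The section Interim analyses {21b} of the protocol article states that "an interim analysis will be performed after enrolment of 42 (50%) patients". The look is to establish that AE rates are acceptable, meaning "within the normal rate of complications related to PRC/FCA". On blinding it says: "The interim analysis will be carried out blinded to the group allocation unless a clear deviation in the incidence of AEs is found", and it continues "in which case the allocation will be unveiled, and the study discontinued". It does not say whether the counts are pooled or shown by masked arm.

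Three other parts of the article bear on this:

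- **Adverse events (under Outcomes).** Non-union and implant-related complications are listed as AEs, alongside events that either procedure can cause.
- **Discussion.** PRC "avoids the risk of bony non-union, implant loosening, breakage, and removal". The background section adds that some study groups prefer PRC for postoperative complications.
- **Sections {21a} and {22}.** A DSMC of two clinicians and a statistician is set up. "The DSMC will evaluate the safety of the trial based on major adverse event reporting", and "all major AEs will be documented and reported to the DSMC within 5 working days". Neither section mentions the interim look, and {21b} does not mention the DSMC.

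**The concern.** The stated purpose is to compare observed AE rates with what is normal for each operation. By the protocol's own account the operations differ in which AEs they can produce, so a total rate that is ordinary after FCA could be an excess after PRC. To apply a norm that depends on the procedure, one must know the procedure, and the look withholds it.

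The consequence is also fixed in the text. Allocation is learned together with discontinuation, so by-arm data have no part in the decision as written.

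Two errors become more likely. A real excess after one procedure may be diluted, or put down to the other procedure. Or the trial may be ended on a count that a table by procedure would have explained.

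**Working it through.** **The plan's own figure.** The planned total is 84, and 0.5 × 84 = 42, so the interim size reproduces. With 1:1 allocation this is about 42 / 2 = 21 per arm.

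**Inputs that are assumptions.** The protocol gives no AE rates or limits. The rates below are illustrative, all 42 patients are treated as fully observed, and a flag limit is the smallest count with a false-alarm chance of at most 5%.

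**Method.** For a PRC-only look, the chance of a flag is P(X ≥ r) with X ~ Bin(21, p). For a pooled look it is P(X + Y ≥ r) with X ~ Bin(21, p_PRC) and Y ~ Bin(21, p_FCA), computed exactly by convolution.

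**Norms that differ by procedure**

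| Assumed norms (PRC / FCA) | What happens | Pooled limit | Pooled flag | PRC-only limit | PRC-only flag |
|---|---|---|---|---|---|
| 10% / 20% | PRC 30%, FCA 20% | ≥11 of 42 | 48.8% | ≥6 of 21 | 63.7% |
| 5% / 15% | PRC 15%, FCA 15% | ≥9 of 42 | 16.9% | ≥4 of 21 | 38.9% |
| 10% / 20% | PRC 20%, FCA 10% | ≥11 of 42 | 4.0% | ≥6 of 21 | 23.1% |

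False-alarm rates are 4.0% (pooled) and 1.4% (PRC-only) in the first and third rows, so the comparison there leans in favour of the pooled look. They are 1.9% for both in the second row. In the third row the expected pooled count is 21 × 0.20 + 21 × 0.10 = 6.3, the same as under the norms (21 × 0.10 + 21 × 0.20 = 6.3). The pooled look therefore flags no more often than by chance.

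**One common norm, 20-point excess in one arm.** Pooled and known-arm looks use a 5% limit. With masked arms, each arm is checked at 2.5%.

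| Common norm | Pooled | Masked A/B | Arm known |
|---|---|---|---|
| 10% | 47% | 64% | 64% |
| 20% | 37% | 48% | 65% |
| 30% | 29% | 34% | 50% |

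**Masked arms when the norms differ.** Suppose A shows 20% and B shows 10%. With norms of 10% (PRC) and 20% (FCA), this is as expected if A is FCA, but PRC is at twice its norm if A is PRC. The masked totals cannot separate the two. For size, take norms of 10% (PRC) and 30% (FCA), with PRC actually at 30%. Judged as PRC (limit ≥6 of 21), the arm is flagged 64% of the time. Judged against the FCA norm (limit ≥11 of 21), it is flagged 2.6% of the time.

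**The rule, step by step.** A clear deviation is found while blinded, the allocation is unveiled, and the study is discontinued. The sentence contains no review of by-arm data between the second and third steps and no alternative outcome after unveiling.

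**The case against.** A reader might infer that the look is unable to see an excess in one arm. The figures do not support that. The pooled look still flags a tripled PRC rate about half the time, and masked A/B tables can show an imbalance. A table by event type would often reveal which arm is FCA, because non-union and implant events belong to it alone. Small numbers also limit any look: with 21 per arm, even the PRC-only look flags a doubling from 10% to 20% only 23% of the time. The third row of the first table needs a contrived pairing, with PRC doubling while FCA halves.

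A reader might also infer that any signal ends the trial, or that this is the only safety oversight. Neither holds. The text requires a clear deviation, which implies judgement. The DSMC receives major AEs throughout, the operating surgeon reviews follow-up CBCTs knowing the procedure, and individual patients can be unblinded for safety.

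Finally, a journal article condenses the full protocol. That {21b} does not name the DSMC is, taken alone, only silence, and nothing says the DSMC is excluded. The missing rates and thresholds are likewise commonly left to other documents. Keeping an interim look blinded is a recognised choice.

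All of this stands, and it limits the size of the point. It does not answer two things that the article states outright: the benchmark is what is normal for the procedures while the procedure is withheld, and unveiling is joined to discontinuation. A charter that inserted a by-arm review before the decision would depart from that sentence.

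**Conclusion.** The concern holds as one of reduced sensitivity and unreliable interpretation, together with a stopping sentence that leaves no place for by-arm review. Under the assumed rates, the pooled look flags an excess in one arm 49% against 64% of the time, or 17% against 39%, compared with a PRC-only look. With masked arms the loss ranges from none to moderate when the norms are equal. It is near total only when the norms differ and an arm is judged against the wrong, higher one (2.6% against 64%).

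The direction follows from the protocol's own description of the AE profiles. The sizes depend on rates that the protocol does not supply. The look tests no efficacy hypothesis and leaves the PRWE comparison unaffected. The point therefore deserves correction, but it is not a critical defect.

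**What to change.** Four changes, all of wording:

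1. At the interim, the DSMC receives, through its own statistician, a closed table of AEs by actual procedure, so that each arm can be read against its own reference rate.
2. Showing the allocation to the DSMC is separated from any decision on the trial's future.
3. The DSMC reviews the by-arm data and makes its recommendation first. Any decision follows that review.
4. Sections {21b}, {21a} and {22} are reconciled, so that the interim look on all AEs and the DSMC's review of major AEs form one process.

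Patients, recruitment investigators, outcome assessors and the trial biostatistician stay blinded. No stopping limit is proposed here.

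The committee and its statistician are already planned, so the cost is an amendment to the protocol and charter text. The one downside is that a closed unblinded table will exist and must be kept within the DSMC.
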